A study questionnaire will be used to obtain data, and a total of five test parameters will be monitored. The questionnaire and tests will be performed at every visit, and it will take about 30 minutes. The questionnaire and tests will be performed at Kyung Hee Bi, Che, Dam Korean Medicine Clinic, and the PI will be in charge of distributing and collecting the questionnaire and performing tests.

| Item | Screening and enrollment | Treatment phase | | F/U |
| --- | --- | --- | --- | --- |
|  |  | 4wks | 8wks | 12wks |
| Visit | Visit 1 | Visit 2 | Visit 3 | Visit 4 |
| Visit window | 0주 | Week 4 (±7 days) | Week 8  (±7 days) | Week 12  (±7 days) |
| Informed consent | ○ |  |  |  |
| Sociodemographic information | ○ |  |  |  |
| VS and physical examination | ○ | ● | ● |  |
| Compliance with pre-visit instructions | ○ | ● | ● |  |
| Medical history·treatment history·medication history | ○ |  |  |  |
| Inclusion and exclusion criteria | ○ |  |  |  |
| Blood test | ● | ● | ● |  |
| BP and pulse measurement | ○ | ● | ● |  |
| 3D BP waveform test | ● | ● | ● |  |
| European Quality of Life Five Dimension Five Level Scale (EQ-5D-5L) | ● | ● | ● |  |
| Modified SMS prescription and dispensing | ● | ● |  |  |
| Monitoring of herbal medicine adherence and dosage |  | ● | ● |  |
| Monitoring of AEs |  | ● | ● | ● |
| Changes in Medical history·treatment history·medication history ** |  | ● | ● | ● |
| Conclusion of case* |  |  |  | ● |

Table 2. Summary of study data collected by timeline

* Conclusion of case: collected after visits are completed or participant is discontinued

** Changes in Medical history·treatment history·medication history: Collect information upon changes in Medical history·treatment history·medication history since the visit

● Tests performed only on those who qualify per the inclusion/exclusion criteria

eCRF will be identical to the paper-based CRF, and the Mytrial program at NIKOM will be used to establish the eCRF.

Modified intervention records: if the treatment interventions are changed mid-way, the changes will be recorded in the modified intervention record section of the CRF.

Concomitant drugs and treatment: Concomitant drugs and treatment will be recorded in the respective section in the CRF.

1. Management of human-derived materials

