This study is an observational study collecting clinical data and observing the clinical course of patients taking modified SMS, and there are no interventions other than the herbal medicine regimen or any additional tests required for study participation. If an AE occurs nonetheless, the herbal medicine regimen will be discontinued, and the patient will be observed and treated as necessary until the event is resolved per the general treatment protocol at Kyung Hee Bi, Che, Dam Korean Medicine Clinic.

Measures taken for abnormal blood test results: liver function test including aspartate transaminase (AST), Alanine transaminase (ALT), Gamma glutamyl peptidase (GGT), and total bilirubin, as well as BUN, creatinine, total cholesterol, and glucose are measured on visits 1, 2, and 3. Per the general treatment protocol at Kyung Hee Bi, Che, Dam Korean Medicine Clinic, additional use of herbal medicine regimen is suspended if the levels rise more than twofold, along with the standard medical measures (including tests) for f/u.

Given the minimal anticipated side effects, the study is not expected to have substantial safety issues. As a rule, safety parameters are monitored, and any incidence of AEs will be notified to the PI and co-investigators. Upon onset of an AE, appropriate medical measures will be taken until recovery.

1. Evaluation of safety parameters

Safety evaluation will be performed for all AEs that occur during the study period. The rate of AE, rate of AE that led to discontinuation, and rate of SAE are reported. For the rate of AEs, all AEs and AEs associated with Korean medical care and intervention will be presented.

VS or blood test results will be reviewed comprehensively to determine normal/abnormal results, and items deemed clinically significant by the clinician can be analyzed statistically as necessary.

1. Data analysis and statistical methods

Efficacy evaluation will be performed using the FAS. Safety data will be analyzed with the safety set. All analyses will be conducted using the SAS Version 9.4 (SAS Inc, Cary, NC) software, and all statistical tests not defined separately will be performed as a two-tailed test and 5% significance level. Any missing values in the FAS will be imputed using the Last Observation Carried Forward (LOCF) method for the efficacy evaluation. All other data will be analyzed as is.

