Full Analysis Set(FAS): Per the Intention-to-Treat (ITT) principle, FAS includes participants who have received the herbal medicine preparation at least once and have had at least one measurement of the primary outcome measure

Safety Set (SS): Includes participants who have received the herbal medicine preparation at least once and have had at least one safety-related f/u

For demographic and baseline data, categorical data will be presented as n (%), and continuous data will be presented as mean±SD.

For efficacy parameters, continuous variables will be analyzed with paired t-test or Wilcoxon signed rank test, and categorical variables will be analyzed using the McNemar test or McNemar Exact test depending on their normality.

For safety parameters, adverse drug reactions (ADRs), SAEs, and serious ADRs will be presented as n (%), and differences across time points will be analyzed using the McNemar test or McNemar Exact test.

ANCOVA model will be used for analysis with sociodemographic factors that may affect HTN, such as sex, age, and use of antihypertensive drugs, included as covariates.

1. Withdrawal of consent and discontinuation
2. Discontinuation criteria

Participants may be discontinued from the trial in the following instances:

- Participants or their legal representatives requests discontinuation or participant withdraws consent due to unsatisfactory treatment effects during the study period
- Violation of inclusion criteria or meeting exclusion criteria
- Failure to take the modified SMS even once during the observational study period, despite giving consent and meeting eligibility criteria
- Occurrence of SAE related to the herbal medicine or AE making continuation in the study difficult
- Change of prescription during study
- Participant’s violation of study plan
- Lost to f/u during study period
- Other reasons due to which continuation of study is deemed inappropriate by the investigator

1. Study termination criteria

Upon occurrence of SAE suspected to be caused by the investigational drug, the PI notifies the joint IRB within 24 hours and terminate the study.

The clinical trial may be terminated prematurely in the following cases:

- Harmfulness of investigational product is discovered
- Moderate or severe AE deemed to have a relationship with the clinical trial occurred in more than 25% of the entire study population
- Study poses threat to the safety and well-being of study participants

1. Withdrawal of consent

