Even after voluntarily consenting to participate, participants may withdraw their consent at any time without any disadvantages. If a participant wishes to withdraw their consent or meets the criteria for study discontinuation, their personal information and relevant data will be excluded from the analysis and will be discarded immediately.

1. Risks and benefits for study participants
2. Potential risks

The study lacks a control group, and only routine intervention and tests are involved; thus, there is no added risk from study participation.

During routine treatment, modified SMS has little risk for side effects or tolerance, but gastrointestinal symptoms (indigestion, heartburn) and autonomic nervous system symptoms (palpitations) may occur.

Since no additional interventions or tests are involved, there will be no cases of injuries caused by participation in the study. However, issues arising from routine medical care can be compensated according to the clinic’s malpractice liability insurance policy.

1. Potential benefits

Since the treatment protocol for modified SMS at Kyung Hee Bi, Che, Dam Korean Medicine Clinic is followed, there is no direct benefit to participants from participating in the study.

However, by participating in the study, participants contribute to gathering information on the effectiveness of modified SMS in improving HTN and observing its progress, which can aid in the future development of Korean Medicine-based treatments for HTN.

1. Risk/benefits analysis

Considering the potential risks and potential benefits, there is a low risk of side effects and no additional benefits to treatment. However, there are also no additional risks posed by study participation. Thus, the study is deemed to pose minimal risk to the participants.

1. Compensation for study participation

The compensation for the study participants (e.g., transportation) is 50,000 KRW for each visit (1, 2, 3) for a total of 150,000 KRW. Visit 4 is a telephone f/u, so there is no compensation.

Participants’ bank account numbers will be additionally collected for payment of the compensation.

1. Measures to protect participants’ safety and personal information
2. Information collected for routine medical care and patient management

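### The rule in Section 17.C to discard data of anyone meeting a discontinuation criterion contradicts the FAS, safety set and all-AE rules; applied literally, it removes serious ADRs and AE-related study exits from the analysis.

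*Protocol*

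**What the plan says.** Section 17.C (Withdrawal of consent) has two triggers for removing data. One is the wish to withdraw consent. The other applies when a participant "meets the criteria for study discontinuation, their personal information and relevant data will be excluded from the analysis and will be discarded immediately".

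Section 17.A (Discontinuation criteria) lists among its criteria "Occurrence of SAE related to the herbal medicine or AE making continuation in the study difficult". Loss to follow-up, a change of prescription and violation of the study plan are also on the list.

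Other sections assume that these participants' data remain available:

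- Section 14.G (Evaluation of safety parameters): "Safety evaluation will be performed for all AEs that occur during the study period". It adds: "The rate of AE, rate of AE that led to discontinuation, and rate of SAE are reported".
- Section 16 (Data analysis and statistical methods), on safety summaries: "For safety parameters, adverse drug reactions (ADRs), SAEs, and serious ADRs will be presented as n" and per cent.
- Section 16, safety set: "Includes participants who have received the herbal medicine preparation at least once and have had at least one safety-related f/u". Discontinuation is not a ground for exclusion.
- Section 16, FAS: at least one intake of the medicine and at least one primary outcome measurement, under the ITT principle, with missing values filled by LOCF.
- Section 11.F, notes to Table 2: "Conclusion of case: collected after visits are completed or participant is discontinued".

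**The concern.** Exploring safety is a stated aim (Purpose of study), and the data are meant to inform later studies. The events that matter most for that are related serious events and AEs that drive people out of the study. These are the events that bring a participant under the discard rule. One part of the protocol promises to report them, and another orders the underlying data to be excluded and destroyed.

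A site that follows 17.C to the letter would produce a safety table that looks cleaner than what happened. A later analysis plan could redefine the analysis sets, but it could not restore records already destroyed at the site. The same sentence also takes discontinued participants out of the efficacy analysis, which the ITT-based FAS and LOCF are meant to prevent.

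**Working it through.** **The plan's own figure.** Section 9 wants data from 20 participants at 33% dropout: 20 / (1 − 0.33) = 29.85, rounded up to 30. This reproduces and is not in dispute. It implies about 30 × 0.33 = 9.9, so about 10 dropouts.

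**Step 1: which participants the rule reaches.** The word joining the two triggers in 17.C is *or*, so meeting a 17.A criterion suffices without withdrawal of consent. 17.A says that participants *may* be discontinued, but 17.C acts on meeting the criteria, so that discretion does not narrow the discard.

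**Step 2: serious ADRs.** A serious ADR is an SAE related to the medicine, which is itself a 17.A criterion. Under 17.C every such participant is removed, so the numerator is 0. Section 17.B has the PI terminate the study on a suspected related SAE, so the realistic case is one event. With n in the safety set at that point, 1/n becomes 0/(n − 1):

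- n = 20 (assumed): 1/20 = 5.0% becomes 0/19 = 0%
- n = 30 (all enrolled and followed): 1/30 = 3.3% becomes 0/29 = 0%

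**Step 3: AEs leading to discontinuation, read as study exit.** If d of 30 leave for an AE, the rate is d/30 when they are kept and 0/(30 − d) under 17.C:

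- d = 1: 3.3% becomes 0%
- d = 2: 6.7% becomes 0%
- d = 3: 10.0% becomes 0%

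The protocol gives no expected rate. For assumed true rates p, the chance of at least one such exit among 30 is 1 − (1 − p)^30, which is 60% at p = 3%, 79% at 5% and 96% at 10%.

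**Step 4: overall AE rate.** Let k be the number with any AE and d the number of those who meet the AE criterion. The reported rate is (k − d)/(n − d). As an illustration, assume k = 6 and no other discards:

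| n | Rate with all kept | d = 1 | d = 2 | d = 3 |
|---|---|---|---|---|
| 30 | 6/30 = 20.0% | 5/29 = 17.2% | 4/28 = 14.3% | 3/27 = 11.1% |
| 20 | 6/20 = 30.0% | 5/19 = 26.3% | 4/18 = 22.2% | 3/17 = 17.6% |

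Discards for other reasons, such as loss to follow-up, also shrink the denominator and could move this rate either way. They do not change the zeros in Steps 2 and 3.

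**Step 5: efficacy.** Loss to follow-up is a 17.A criterion, so up to about 10 of 30 participants could be discarded. Those among them who meet the FAS definition should, under Section 16, be analysed with LOCF. How many that is depends on when they leave, which the protocol does not give.

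**Step 6: which rule prevails.** Sections 14.G and 16 and the Table 2 note keep these participants; 17.C removes them. No section ranks the rules.

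**The case against.** The strongest reply is that the protocol contradicts itself, so the zeros are not inevitable. A team that follows Section 14.G and the safety set definition would keep the events. This stands: the zeros are conditional on a literal application of 17.C.

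Four further points narrow what may be inferred.

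- A reader might infer that serious ADRs could accumulate unseen in a completed 30-person report. The documents do not support that. SAEs are reported through the e-IRB system (Section 14), and Section 17.B requires notice to the joint IRB within 24 hours and termination. What would be lost is the event in the study's own rates.
- The zero for AEs leading to discontinuation depends on reading that phrase as study exit. Section 14.F uses the same word for stopping the herbal regimen. On that reading the rate need not be 0, because someone may stop the product and remain under observation. The serious ADR count is unaffected by this choice.
- A reader might infer that the stopping guideline, "Moderate or severe AE deemed to have a relationship with the clinical trial occurred in more than 25% of the entire study population", would also lose its worst cases. Nothing says that this count is taken from retained data: it refers to the whole study population, and AEs are notified to the PI.
- A reader might infer that every copy is destroyed. Section 20 keeps data sent to the Mytrial system for 10 years, and the protocol does not say whether the discard reaches that copy. Even if it survives, 17.C separately excludes it from the analysis.

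Two other replies do not help. The sentence stands under a heading on withdrawal of consent, but it names discontinuation expressly. Nor is this a detail properly left to an analysis plan, because the protocol itself fixes the disposal of data at the site.

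**Conclusion.** The point holds as an unresolved internal contradiction with a damaging literal reading. If 17.C is followed as written, serious ADRs are counted as 0 in the study's own analysis, and so are AEs leading to discontinuation where that means study exit. The overall AE rate and the efficacy FAS also lose participants whom Section 16 would keep.

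The two zeros follow from the wording and rest on one condition, that 17.C overrides Sections 14.G and 16; the second also needs the study-exit reading. The figures for the overall AE rate rest on assumed counts and only show scale. AEs that do not meet a 17.A criterion, including unrelated SAEs that allow continuation, would still be counted for participants not discarded for another reason.

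The change should be made: the defect is plain in the text, the correction is short, and destruction of site records may not be reversible.

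**What to change.** In Section 17.C, delete the second trigger (the limb on meeting the discontinuation criteria), so that the discard applies to withdrawal of consent only. Then add:

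*Data collected up to discontinuation for reasons other than withdrawal of consent are kept and analyzed in the FAS and the safety set wherever the participant meets the definition of that set.*

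The report should also state whether its rate of AEs leading to discontinuation refers to stopping the product or leaving the study. The clinic's own rule for stopping the regimen after an AE need not change.

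The cost is a protocol and IRB amendment and a matching check of the consent form, which is not among the documents. If that form repeats the discard promise, it needs the same edit, and participants already enrolled may need to re-consent. Visits, sample size and CRF are unchanged, since a case conclusion is already collected for discontinued participants. AEs of participants who withdraw consent would still be lost.

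### The consent-withdrawal section discards the data of anyone who meets a discontinuation criterion, which contradicts the Full Analysis Set with LOCF, the Safety Set and the planned rate of AEs leading to discontinuation

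*Protocol*

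**What the plan says.** All references are to the protocol, numbered as in its table of contents.

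- **Section 17.C, Withdrawal of consent.** The rule has two triggers. One is withdrawal of consent. The other is that the participant "meets the criteria for study discontinuation, their personal information and relevant data will be excluded from the analysis and will be discarded immediately".
- **Section 17.A, Discontinuation criteria.** The list includes "Lost to f/u during study period", "Occurrence of SAE related to the herbal medicine or AE making continuation in the study difficult" and "Change of prescription during study", as well as violation of the study plan.
- **Section 16, analysis sets.** For efficacy: "Per the Intention-to-Treat (ITT) principle, FAS includes participants who have received the herbal medicine preparation at least once", with at least one measurement of the primary outcome also required. For the Safety Set: "Includes participants who have received the herbal medicine preparation at least once and have had at least one safety-related f/u". Neither definition excludes a participant for discontinuing.
- **Section 16, missing data.** "Any missing values in the FAS will be imputed using the Last Observation Carried Forward (LOCF) method for the efficacy evaluation".
- **Section 14.G, Evaluation of safety parameters.** "The rate of AE, rate of AE that led to discontinuation, and rate of SAE are reported".
- **Section 11.F, Table 2.** A case-conclusion record is completed for discontinued participants as well as for those who finish.

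**The concern.** The protocol fixes who is analysed in two ways that cannot both be applied. Sections 14.G and 16 are written for a study that keeps its early leavers: LOCF needs a last observation to carry forward, and a rate of AEs leading to discontinuation needs discontinued participants in its numerator. Section 17.C removes those people and their data.

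The primary result is the change in mean sitting systolic BP (MSSBP) from visit 1 to visit 3 in one unblinded group. No comparison group would offset selective removal after dosing. If those removed had smaller falls than the rest, the mean fall is overstated; if larger, it is understated. On safety, those who leave because of an AE are the ones most needed in the count. These estimates are meant to inform a later randomised trial.

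**Working it through.** **1. The protocol's own figure.** The sample-size section aims for data from 20 participants with 33% dropout: 20 / (1 − 0.33) = 29.85, rounded up to 30, as stated. Expected losses are 30 × 0.33 = 9.9, about 10, leaving 30 × 0.67 = 20.1, about 20. Early leaving is therefore the expected course for a third of the sample.

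**2. The two rules side by side.**

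| Participant | Under section 16 | Under section 17.C |
| --- | --- | --- |
| Dosed, seen at visit 2, then lost | In FAS, visit 2 value carried to visit 3; in Safety Set | Excluded, data discarded |
| Dosed, never seen after visit 1 | In FAS only if the visit 1 reading counts as the required measurement, which the text does not settle | Excluded, data discarded |
| Dosed, leaves the study because of an AE found at follow-up | In Safety Set; in FAS if the measurement condition is met | Excluded, data discarded |
| Dosed, prescription changed after visit 2 | In FAS and Safety Set | Excluded, data discarded |
| Never dosed | In neither set | Excluded; the rules agree |

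The rules agree for the never-dosed. They conflict for dosed participants who satisfy the section 16 conditions and also meet a 17.A criterion.

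**3. Efficacy: what can and cannot be sized.**

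- *If the visit 1 reading counts as the measurement*, section 16 analyses 30 and section 17.C about 20, assuming every week-4 returner completes. Carrying baseline forward gives ten changes of zero, so the two means differ by a factor of 30/20 = 1.5 whatever the effect. That is a product of the imputation and does not estimate bias.
- *If a later reading is required*, the FAS is about 20. Let k be the number lost after visit 2, and d the completers' mean change minus the leavers' carried-forward mean change. The FAS mean is [(20 − k) × completers' mean + k × leavers' mean] / 20, so the 17.C mean differs from it by (k/20) × d. The protocol gives neither k nor d. As an assumed range only, take loss after visit 2 of 0 to 33% (20 × 0.67 = 13.4 stay, so k runs from 0 to 7) and d of 5 mmHg in either direction. The shift is then 0 to 7/20 × 5 = 1.75 mmHg, in either direction.

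**4. Safety.** Suppose all 30 are in the Safety Set and k of them leave the study because of an AE. The rate should be k/30. After discarding it is 0/(30 − k).

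| k | Rate as section 14.G intends | Rate after section 17.C |
| --- | --- | --- |
| 1 | 1/30 = 3.3% | 0/29 = 0% |
| 2 | 2/30 = 6.7% | 0/28 = 0% |
| 3 | 3/30 = 10.0% | 0/27 = 0% |

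The values of k are illustrative. The zero is not: the rule empties the numerator for any k. The overall AE rate loses the same participants.

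**The case against.** **The clause may be a slip.** It stands under a heading about consent withdrawal, where discarding data is defensible, and 17.A says only that participants may be discontinued. This is a fair reading of intent. But 17.C names the discontinuation criteria as a separate trigger, is worded as meeting them rather than as an investigator's decision, and asks for immediate action. Nothing elsewhere narrows it. If discretion does apply, the investigator in an unblinded study decides whose data survive.

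**The AE rate is not always zero.** A reader might infer that the rate of AEs leading to discontinuation would be zero whatever happened. The document does not support that. Section 14.F stops the herbal regimen after an AE while the patient stays under observation, and such a participant need not meet a 17.A criterion. Section 14.G does not say whether its rate means stopping the medicine or leaving the study. The forced zero holds only for the second meaning.

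**Discarded data may survive elsewhere.** A reader might also infer that the loss could never be undone. Section 20 keeps data provided through Mytrial for 10 years, and BP and blood tests are also routine-care records. Whether these escape the discard rule is unclear, so irrecoverability should not be asserted. Even so, 17.C excludes the data from the analysis.

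**The stakes are limited.** The study has 30 participants, is exploratory and disclaims determining efficacy. A suspected drug-caused SAE goes to the IRB within 24 hours and terminates the study (section 17.B). This bounds the importance and the risk to participants, but IRB reporting does not repair the study's own rates.

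**Conclusion.** The contradiction is in the current text, and no passage in the protocol resolves it. Followed as written, section 17.C removes dosed participants whom section 16 retains, allows bias in the MSSBP change in either direction, and under-counts AEs. The rate of AEs leading to study discontinuation would be zero by construction; AEs that stop only the regimen, with the participant still followed, could still be counted. It should be fixed, and it is no more serious than that.

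The number at risk rests on the protocol's 33% dropout, about 10 of 30. It is based on general clinic re-attendance, and whether those people would enter the FAS depends on which measurement qualifies. No BP shift can be derived: the factor of 1.5 and the 1.75 mmHg above rest on assumptions and should not be quoted as the bias.

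A reader might extend the point to section 11.C, which leaves cases with an altered formula or added acupuncture out of the analysis, and see a second conflict with the FAS. That sentence reads naturally as separating the clinic's tailored prescribing from the fixed formula studied here, so the document does not establish one.

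**What to change.** Reword section 17.C in two respects. First, limit exclusion and discarding of data to participants who withdraw consent for the use of their data. Second, state that data collected up to discontinuation for any other reason are kept and analysed in the FAS and Safety Set as section 16 defines them.

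This keeps the protection for those who withdraw that consent, and brings 17.C into line with section 16, the AE rates in section 14.G and the case-conclusion record in Table 2. The cost is a wording change only, with no extra patients, visits or tests.
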